#### Follow-Up Telephone Sessions

Seven follow-up telephone sessions occur weekly for the first month (sessions 2-4) and then biweekly for the second and third months (sessions 5-8). Each session begins with an evaluation of the previous week’s problem, including the veterans’ perceptions of the effectiveness of the strategies used. If needed, problem-solving guidance is provided or reinforced via verbal feedback from the NI. If the problem improves and no further problem-solving is required, the NI works with the veterans to establish a maintenance plan using rational problem-solving strategies. Veterans then repeat the card sorting task to identify new problems and the iterative five-step, problem-solving process starts over. Both current and new problems are identified by the veterans and examined during each follow-up telephone session. Each follow-up session lasts approximately 30 minutes. Figure 2 provides an overview of the study and associated major activities.

**Figure 2 figure2:**
[figure not shown]
Study overview.

### Intervention Fidelity

Strategies to enhance intervention fidelity are based upon the National Institutes of Health Behavior Change Consortium recommendations [39]. Standardized training for research staff who are conducting inclusion and exclusion screening, data collection, and intervention sessions occurred before study implementation to ensure adequate skill acquisition for the defined roles. The primary investigator trained staff initially until a minimum of 90% accuracy was achieved in covering the key elements of the defined role using role-playing, scenarios, and scripts. Fidelity checks of eligibility screening and informed consent, data collection contacts, and intervention sessions are also performed by the primary investigator every three months using a checklist of key elements for the specific activity to ensure that 90% of core elements are being consistently performed. Retraining of research staff occurs as needed to ensure that they meet the 90% criterion.

### Data Analysis

#### Preliminary Analyses

Descriptive statistics will be computed on all time-invariant and time-varying study variables. Cronbach α values will be calculated for all measures containing multiple items to assess internal consistency. In the case that internal consistency is low (α<0.6), an if-item-deleted analysis will be performed, and items that are not a good indicator for the underlying construct will be excluded.

#### Main Analyses

Multilevel growth curve modeling will be used for the testing of aim 2 or the evaluation of the effectiveness of CARE-HF. For each outcome variable, a series of models will be estimated and compared using incremental fit indices, including the Akaike information criteria and the Bayesian information criteria. The first model is an intercept-only model. Then, a growth curve model with a linear growth component will be estimated. Finally, a model with a quadratic growth component will be tested. The multilevel modeling and restricted maximum likelihood estimation method will be used in R (R Foundation for Statistical Computing) [40]. This method can deal with dropouts and missing data without excluding incomplete cases. In addition to fixed effects, random effects will be estimated.

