### Purpose, Aims, and Hypotheses

The overall purpose of this study is to adapt to the rural sociocultural context and test the efficacy of a tailored, telephone-based intervention (CARE-HF) to support the physical and mental health of rural veterans by enhancing disease self-management and coping processes. To accomplish this goal, our research aims are to:

Adapt the CARE-HF intervention content to the rural sociocultural context using findings from preliminary qualitative research.Examine the effectiveness of the CARE-HF intervention on study outcomes (HF self-care, HF symptoms, health care utilization, depressive symptoms, anxiety, health-related quality of life, stress, resilience, and coping), process (problem-solving), and antecedent (social support) in a sample of rural veterans with HF (N=100) at baseline and 3, 6, 12, and 18 months from baseline.

Our hypotheses are as follows:

Hypothesis 2a: Increases in HF self-care, health-related quality of life, resilience, coping, and problem-solving will be noted at 3 months from baseline and sustained throughout the 18-month follow-up period.Hypothesis 2b: Decreases in HF symptoms (frequency, severity, and interference with physical activity and enjoyment of life), health care utilization, depressive symptoms, anxiety, and stress will be seen at 3 months from baseline and sustained throughout the 18-month follow-up period.

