### Design and Sample

This study includes a repeated-measures, single-group design. Veterans are recruited from Veterans Administration home-based cardiac rehabilitation clinics, cardiology clinics that serve veterans, veterans-based community resource centers, and social media campaigns using study flyers. Veterans with HF (N=100) will be recruited over 3 years, with the anticipated enrollment of 5 or more veterans per month. The desired sample size was based on a power analysis for repeated-measures ANOVA with 5 time points, α=.05, a medium effect size (f=0.25), and 80% power, plus oversampling for potential attrition (20%) estimated from studies involving patients with HF [17,18]. Veterans are eligible for participation if they (1) have a diagnosis of HF; (2) are aged 18 years or older; (3) have New York Heart Association functional class II-IV HF; and (4) can read, write, and communicate verbally in English, and excluded if they have a history of cognitive impairment.

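### The sample size is powered for an omnibus ANOVA that the plan does not run, and the linear and quadratic growth models that replace it cannot represent the hypothesised change by 3 months that is then held

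*Protocol article*

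**What the plan says.** Three parts of the protocol article bear on this.

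- **Design and Sample.** "The desired sample size was based on a power analysis for repeated-measures ANOVA with 5 time points", with "α=.05, a medium effect size (f=0.25), and 80% power". The number was then raised: "plus oversampling for potential attrition (20%) estimated from studies involving patients with HF". The target is 100 veterans, so 80 completers at 20% attrition.
- **Main Analyses.** The section opens with this statement: "Multilevel growth curve modeling will be used for the testing of aim 2 or the evaluation of the effectiveness of CARE-HF". An intercept-only, a linear and a quadratic model are compared by AIC and BIC for every outcome, using restricted maximum likelihood. No test with time as a categorical factor is described.
- **Purpose, Aims, and Hypotheses.** Under Hypotheses 2a and 2b, improvements "will be noted at 3 months from baseline and sustained throughout the 18-month follow-up period" (2a; 2b is worded almost identically).

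Measurements fall at baseline and at 3, 6, 12 and 18 months (Data Collection). The Limitations section says that the long follow-up serves to judge whether the effect lasts and whether booster sessions are needed.

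**The concern.** A repeated-measures ANOVA compares five unconstrained means on 4 degrees of freedom. A linear growth term uses 1 degree of freedom and a linear-plus-quadratic model uses 2. They use the same data but look for different signals. Power computed for the first carries over to the others only if the true time course is close to a straight line or a parabola.

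The trial's own hypotheses describe neither. A change that arrives by 3 months and then stays is a step followed by a plateau. Two things are at stake. First, the power figure behind N=100 says nothing definite about the chance that the planned analysis detects the hypothesised effect. Second, the fitted curve may give the wrong answer on sustainability, which is the reason for following veterans to 18 months.

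**Working it through.** **Inputs.** From Design and Sample: five time points, α=0.05, f=0.25, 80% power, 20% attrition, N=100 (100 × 0.80 = 80 completers). From Data Collection: months 0, 3, 6, 12, 18. From the hypotheses, as a reading of the text: pattern y = (0, 1, 1, 1, 1). Not in the article: within-person correlation ρ, sphericity parameter ε, and how time is coded.

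**Step 1. Reproduce the sample size.** With noncentrality λ = f²·N·5/(1−ρ) and degrees of freedom 4 and 4(N−1) under sphericity, the smallest N for 80% power is:

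- ρ=0: 40 completers, 40/0.8 = 50 enrolled.
- ρ=0.5: 21 completers, 21/0.8 = 26.25, so 27 enrolled.
- f taken as already including the correlation, λ = f²·(N−1)·4: 50 completers, 50/0.8 = 62.5, so 63 enrolled.

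None gives 100. One variant does: the last convention with ε=0.5 needs 80 completers and 100 enrolled. Since ρ and ε are not stated, this does not show that N=100 is wrong. It does show that the ANOVA power at 80 completers is not known to be 80%.

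**Step 2. Share of the step-and-hold pattern captured.** The mean of y is 0.8 and its total sum of squares is 0.8. For months, the mean is 7.8, Sxx = 60.84 + 23.04 + 3.24 + 17.64 + 104.04 = 208.8, and Sxy = 7.8.

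Linear share: 7.8² / (208.8 × 0.8) = 60.84 / 167.04 = 0.364. Adding the quadratic term raises it to 0.735. With equally spaced wave numbers, the linear share is 2² / (10 × 0.8) = 0.50 and the quadratic share is 0.857.

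Fitted values in months:

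| Month | 0 | 3 | 6 | 12 | 18 |
|---|---|---|---|---|---|
| Hypothesised | 0 | 1 | 1 | 1 | 1 |
| Linear | 0.51 | 0.62 | 0.73 | 0.96 | 1.18 |
| Quadratic | 0.21 | 0.67 | 0.99 | 1.22 | 0.91 |

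The linear model assigns 0.62 − 0.51 = 0.11 of a true change of 1 to the first 3 months and then shows growth up to month 18. The quadratic model peaks near 12 months and falls by 1.22 − 0.91 = 0.31. With wave-number coding, it falls from 1.14 to 0.91 at the end. These fits do not depend on N, f, ρ or ε in a balanced design with a random intercept.

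**Step 3. Power of the growth tests.** Under sphericity, the growth test keeps its share of λ. Error degrees of freedom are 4 × 79 = 316, with time in months:

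| Premise, 80 completers | λ | ANOVA, 4 df | Linear, 1 df | Quadratic, 2 df |
|---|---|---|---|---|
| ANOVA set to exactly 80% | 12.1 | 80% | 0.364 × 12.1 = 4.4: 55% | 0.735 × 12.1 = 8.9: 76% |
| f=0.25 including correlation, λ = 0.0625 × 80 × 4 | 20 | 96% | 77% | 94% |
| f=0.25, ρ=0, λ = 0.0625 × 80 × 5 | 25 | 99% | 85% | 98% |
| f=0.25, ρ=0.5, λ = 25/0.5 | 50 | >99.9% | 99% | >99.9% |

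A simulation of a random-intercept model with 80 completers gave 84.4% (linear) and 97.5% (quadratic) at ρ=0, and 98.8% and 100% at ρ=0.5, in line with the last two rows.

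The first row is not compatible with f=0.25 under sphericity. It needs an effective f of about 0.17 (ρ=0) or 0.12 (ρ=0.5). With wave-number coding, the first row becomes 69% and 83%.

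**The case against.** A reader might infer that the trial is underpowered, at 55% or 76% instead of 80%. The documents do not support that. Those figures require the ANOVA to have exactly 80% power at 80 completers. With the stated f=0.25 and sphericity it has 96% or more, and the growth tests then have about 77% or more (linear) and 94% or more (quadratic). A shortfall below 80% appears only for the linear test under one convention for f.

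Three further points count for the plan. The article says that the sample size was based on an ANOVA calculation; it does not claim 80% for the growth models. The linear model is one step in a series and no stand-alone slope test is named. Even at the low noncentrality of 12.1, AIC would retain the intercept-only model in only about 9% of draws, although BIC would do so in 33% (counting 80 veterans) to 51% (counting 400 records). Finally, a pure step is one reading of the hypotheses. With some further gain after 3 months, such as (0, 1, 1.1, 1.2, 1.3), the shares rise to 0.57 and 0.84. Time coding is also a detail that an article may leave to the full plan.

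All of this stands against any single power figure. It does not remove the mismatch, because the article itself states both the sizing test and the main analysis. Nor does it remove the distortion of shape: under either coding, the quadratic fit to a held effect turns down at the end.

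**Conclusion.** The point holds as a mismatch between the power basis, the analysis model and the hypotheses. The 80% belongs to a test that is not planned. For a step-and-hold pattern, the planned models capture about 36% (linear) and 73% (quadratic) of the between-time variation with time in months, or 50% and 86% with equally spaced waves. A fully sustained effect would appear as continuing growth under one model and as fading after 12 months under the other, which could mislead the decision on booster sessions.

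No claim is made that N=100 is too small. Power for the planned analysis cannot be settled without the within-person correlation, the sphericity assumption and the time coding. All power figures here assume complete data on 80 veterans, sphericity and a pure step. Random slopes, missing visits or a smaller true effect would change them, and the article gives no figures for these beyond the 20% attrition.

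**What to change.** Make the formal test of aim 2 the same multilevel model with time as a five-level factor. Its 4-df test matches the basis of the sample size. Add contrasts that follow the hypotheses: 3 months against baseline for onset, and the later waves against baseline and against 3 months for maintenance. Keep the linear and quadratic growth curves as secondary description of shape. Table 1 shows no baseline measurement of health care utilization, so for that outcome the factor has four levels and the baseline contrasts cannot be formed.

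If growth curves remain the formal test, recompute the power for the specific growth term or terms and restate it in Design and Sample, with the assumed correlation, time coding and time pattern. The conditional figures of 55% and 76% should not be entered as the trial's power.

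The cost is some wording in two paragraphs, one extra model per outcome, and a less parsimonious description of time. No new veterans or data are needed, and the Results section says that analysis will follow study completion.

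### Choosing among growth models by AIC and BIC does not test the directional mean changes stated in Hypotheses 2a and 2b

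*Protocol article*

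**What the plan says.** Under Data Analysis, Main Analyses, the article states: "Multilevel growth curve modeling will be used for the testing of aim 2 or the evaluation of the effectiveness of CARE-HF". For each outcome, "a series of models will be estimated and compared using incremental fit indices, including the Akaike information criteria and the Bayesian information criteria". The sequence is fixed. It opens with no time term ("The first model is an intercept-only model"), moves on to a straight-line trend, and ends by adding curvature ("Finally, a model with a quadratic growth component will be tested"). On estimation: "The multilevel modeling and restricted maximum likelihood estimation method will be used in R". On model terms: "In addition to fixed effects, random effects will be estimated". Which effects are random is not said. The Abstract describes the same comparison.

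Hypothesis 2a (Purpose, Aims, and Hypotheses) predicts increases in a list of outcomes that "will be noted at 3 months from baseline and sustained throughout the 18-month follow-up period". Hypothesis 2b predicts decreases in another list on the same timetable. Alpha .05 appears only in the sample-size sentence of Design and Sample. Statistical significance enters the analysis text only for selecting covariates.

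**The concern.** The hypotheses concern the sign and timing of a mean change. A fit-index comparison asks something else: whether added parameters improve fit by more than a penalty. Three consequences follow.

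- Average worsening favours a growth model as readily as improvement does. In an uncontrolled study of a progressive disease, that is not remote.
- If the intercept-only model is chosen, no time effect is left to estimate or interpret, even where a direct test would have found one.
- If the growth component carries a random slope, the step from intercept-only to linear adds a mean slope, a slope variance and a covariance. Only the first is the hypothesis. Veterans who diverge around a flat mean can be enough for growth to win.

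At stake is whether an outcome is reported as changing, or not changing, after CARE-HF for reasons unrelated to the average veteran.

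**Working it through.** The plan gives no operating figure for this comparison, so there is none to reproduce. The sample size of 100 does not bear on it.

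**Inputs from the article.** Visits at 0, 3, 6, 12 and 18 months; 100 enrolled; 20% attrition, so 100 × 0.8 = 80 veterans and 80 × 5 = 400 observations.

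**Assumed, because not given.** Normal outcomes; complete data; baseline SD 1, split between and within veterans either 0.6/0.4 (setting A) or 0.5/0.5 (setting B); SD of true individual 18-month change varied from 0 to 1 baseline SD; BIC penalty based on the number of observations.

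**1. Best case for the plan: only a fixed slope is added.** The models then differ by one parameter, the mean slope. With no change and identical slopes, the likelihood-ratio statistic under ML is approximately chi-square with 1 df.

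- AIC prefers growth if it exceeds 2: probability 0.157.
- BIC prefers growth if it exceeds ln 400 = 5.99: probability 0.014.
- A two-sided .05 test uses 3.84.

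So neither index works at .05 even here. Simulation at 80 veterans gave 16% and 2%. When individual slopes really vary but are not modelled, runs at 80 or 100 veterans reached up to 33% (AIC) and 12% (BIC).

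**2. A random slope is added too.** Parameters go from 3 to 6. AIC needs an improvement above 2 × 3 = 6, and BIC above 3 × 5.99 = 17.97. With mean change exactly zero (ML, 80 veterans), growth was preferred in:

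| SD of individual 18-month change | Setting A: AIC / BIC | Setting B: AIC / BIC |
|---|---|---|
| 0 | 7% / 0% | 7% / 0% |
| 0.25 | – | 11% / 0% |
| 0.5 | 57% / 6% | 50% / 2% |
| 0.7 (A), 0.75 (B) | 95% / 44% | 95% / 43% |
| 1.0 | 100% / 98% | 100% / 93% |

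Setting A used 600 trials per row; setting B used 400 for the first three rows and 200 for the last two. Further 200-trial runs at 0.5 gave AIC 54% and 61%, and BIC 7%. At 100 veterans (setting B), 0.5 gave 61% / 6%. Under REML (setting B, 80 veterans), 0.5 gave 31% / 3% and 1.0 gave about 100% / 93%.

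A t-test on per-veteran slopes rejected in 6-7% of the 600-trial runs and in 4-11% of the smaller ones. Its true level under these assumptions is 5%, and it did not climb towards 100% as slopes spread.

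**3. Isolating the cause.** With a random slope in both models, so that only the mean slope differs, ML gave AIC 15-22% and BIC 1-4% at every spread tried. The climb in step 2 therefore comes from the unmatched random terms. It is not just the separate problem of comparing REML criteria across different fixed effects.

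**4. Missing a real change.** Take a mean 18-month change of 0.3 SD, slope SD 0.3, setting A. The visit times have mean 39/5 = 7.8 and centred sum of squares 208.8, or 208.8/18² = 0.644 in 18-month units. The variance of one veteran's fitted slope is 0.3² + 0.4/0.644 = 0.711. The standard error of the mean slope is √(0.711/80) = 0.094, and 0.3/0.094 = 3.18. Power is about Φ(3.18 − 1.99) = 0.88. Simulated power was 85-87%. On the same scenario AIC chose growth in 88-90% of trials and BIC in 30-35%. The article gives no precedence when the two disagree.

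**5. Would one linear slope be an adequate replacement?** No. The centred times are −7.8, −4.8, −1.8, 4.2 and 10.2. A gain of 1 unit at 3 and 6 months, lost by 12, gives a slope of (−4.8 − 1.8)/208.8 = −0.032 per month, the wrong sign. A gain only at 12 and 18 months gives (4.2 + 10.2)/208.8 = +0.069, apparent support for 2a without any 3-month change.

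**The case against.** The strongest reply is that the sequence may be no more than ordinary selection of a trajectory shape, after which the chosen model's coefficients are read. Fixed effects are to be estimated, so the mean slope and its sign would be visible, and the hypotheses state the expected direction. A reader might infer that the plan declares efficacy whenever a growth model wins. The article does not say so, and that inference should not be attributed to it.

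A reader might also infer a false-positive rate near 100%. That needs a random slope, which is not stated, and a spread of individual change of about one baseline SD, which the document neither gives nor rules out. At 0.5 SD the BIC rate is only 2-7%, and under REML, the stated method, the AIC rate was 31% in setting B. These limits stand.

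A third reply is that random terms, tests and intervals are details a journal article leaves to the full plan. For those details alone this is fair. It does not dispose of the point, because the article does state a procedure for testing aim 2. That procedure can end in a model with no time effect to read, at an error rate unrelated to the alpha used for sample size. Steps 1 and 4 show this without relying on a large slope spread.

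**Conclusion.** The concern holds in a limited form. The stated AIC/BIC choice is not a test of the directional mean changes in 2a and 2b. In its best case it works at roughly 16% (AIC) or 1% (BIC) instead of 5%, in either direction. If slopes are random, divergence around a flat mean can make growth win: about 50-60% (AIC) and 2-7% (BIC) at an assumed slope SD of 0.5 baseline SD, and above 90% for both at 1.0 (ML, 80 veterans). BIC can also miss real change: about 30-35% against about 86% at 0.3 SD. The simulated sizes rest on normal, complete data and on assumed variances. What the document supports is a mismatch between procedure and hypothesis, with a risk of misreading in both directions. This should be corrected, but it is not a demonstrated false claim.

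**What to change.** In Main Analyses and the Abstract, state that 2a and 2b are judged on prespecified fixed-effect contrasts of mean change: baseline to 3 months, and baseline to 6, 12 and 18 months for persistence. Report each with its sign, 95% CI and alpha .05 test. The model should always keep the time effect and name its random terms. Visit as a five-level factor would serve; under a straight line the four contrasts are 3, 6, 12 and 18 times the same slope and cannot be told apart. Table 1 shows no baseline measurement of health care utilization, so that outcome needs its own stated comparison.

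Keep AIC/BIC for secondary choices: random structure among models with identical fixed effects, or linear versus quadratic shape fitted by ML with the same random structure. Say that preference for or against the intercept-only model is evidence neither of an effect nor of its absence.

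The cost is a few sentences. No data or participants are added, and the Results section says analysis follows study completion. Some outcomes that fit indices would label as growth will be reported as showing no average change.

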**Methods:**

This study involves a repeated-measures, single-group design. The intervention content was adapted and tailored to the rural sociocultural context using preliminary qualitative data and guided by the Theories of Social Problem-Solving and Stress, Appraisal, and Coping. Veterans are recruited from Veterans Administration home-based cardiac rehabilitation clinics, cardiology clinics that serve veterans, veterans-based community resource centers, and social media campaigns. Veterans with HF (N=100) receive the CARE-HF intervention. This nurse-led intervention comprises 8 telephone sessions that use a five-step, problem-solving process to manage common HF problems in the home: (1) identifying the problem and viewing it in a positive manner, (2) goal setting, (3) generating potential strategies for problem management, (4) choosing and implementing strategies to manage the problem, and (5) evaluating strategy effectiveness. Veterans receive initial problem-solving training during the first session, with follow-up sessions focusing on problem-solving skill reinforcement and assisting veterans in applying these principles to manage self-identified, HF-related problems experienced in the home. Data are collected at baseline and 3, 6, 12, and 18 months from baseline on problem-solving and outcomes of interest (ie, HF self-care; HF symptoms; health care utilization; depressive symptoms; anxiety; HF-specific, health-related quality of life; stress; resilience; and coping). Demographic data will be analyzed using descriptive statistics and multilevel growth curve modeling with restricted maximum likelihood estimation to compare a series of models using Akaike information criteria and Bayesian information criteria fit indices while controlling for covariates.

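### AIC and BIC are to compare intercept-only, linear and quadratic growth models on REML fits; these are not comparable, so the preferred trajectory depends on the unit of time and the outcome's scale

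*Protocol article*

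**What the plan says.** Under Data Analysis, Main Analyses, multilevel growth curve modelling is the method for aim 2. For each outcome, "a series of models will be estimated and compared using incremental fit indices, including the Akaike information criteria and the Bayesian information criteria". Three models form the series, in this order: one with no time term, one that adds straight-line change over time, and one that adds curvature, of which the section says that "a model with a quadratic growth component will be tested". On estimation the section says "The multilevel modeling and restricted maximum likelihood estimation method will be used in R" and, on structure, "In addition to fixed effects, random effects will be estimated".

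The Abstract (Methods) joins the two steps in one statement: "multilevel growth curve modeling with restricted maximum likelihood estimation to compare a series of models using Akaike information criteria and Bayesian information criteria fit indices".

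The article mentions no ML fit for the comparison. It names no R package or function, and it gives no unit or coding for time in the model. Data Collection gives the schedule in months: 0, 3, 6, 12 and 18.

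**The concern.** The three models have one, two and three fixed effects. REML does not use the likelihood of the data. It uses the likelihood of error contrasts from which the fixed effects have been removed, and each fixed-effects design defines a different set of contrasts. AIC and BIC taken from REML fits therefore cannot rank models that differ in their fixed effects. They can rank models with the same fixed effects and different random effects, but that is not the series described.

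The comparison shapes the main analysis of aim 2 for every outcome. If it is computed as written, the preferred trajectory can change when time is recoded from months to years. The same standardised change can also be treated differently on two instruments because their scores have different spreads. The scales in Study Measures range from 0-10 symptom ratings to 0-21 (anxiety), 0-60 (depressive symptoms) and 0-100 (self-care).

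**Working it through.** The plan gives no figure for this comparison, so there is none to reproduce.

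**1. Exact effect of the time unit.** For n observations, p fixed effects, design X, covariance V and residuals r,

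-2 log L(REML) = (n - p) ln 2π + ln|V| + ln|X'V⁻¹X| + r'V⁻¹r.

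Recoding time replaces X by XD with D diagonal. V and r are unchanged, and ln|X'V⁻¹X| changes by 2 ln|D|. From months to years, D has entries 1, 1/12 and 1/144:

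- intercept-only: 0
- linear: -2 ln 12 = -4.97
- quadratic: -2(ln 12 + 2 ln 12) = -6 ln 12 = -14.91

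So linear gains 4.97 points on intercept-only, and quadratic gains a further 4 ln 12 = 9.94 on linear, from recoding alone. The ML criterion has no ln|X'V⁻¹X| term and does not move.

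**2. Exact effect of the outcome's scale.** Multiplying the outcome by c multiplies V by c². Then ln|V| rises by 2n ln c and ln|X'V⁻¹X| falls by 2p ln c. Each extra fixed effect therefore gains 2 ln c. With c = 10 this is 4.61. In one simulated data set the linear-minus-intercept REML deviance moved from 7.94 to 3.33, which is the same 4.61.

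**3. One data set** (80 veterans, SD 10, step of 0.625 SD), AIC for intercept-only / linear / quadratic:

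- ML, months or years: 2838.5 / 2819.8 / 2811.0
- REML, months: 2837.3 / 2822.6 / 2821.1
- REML, years: 2837.3 / 2817.6 / 2806.2

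The quadratic's lead over linear is 8.8 by ML. By REML it is 1.5 in months and 11.4 in years.

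**4. How often the choice changes.** Inputs from the article: five waves at 0, 3, 6, 12 and 18 months; N=100 with 20% attrition, so 100 × 0.8 = 80; f=0.25; and a hypothesised change by 3 months that is then sustained. Assumed, because the article does not give them: within-person correlation 0.5, a random intercept only, and the outcome SDs shown. A step d from baseline to four equal later means has a between-time SD of d × √(1/5 × 4/5) = 0.4d, so f=0.25 corresponds to d = 0.25/0.4 = 0.625 SD.

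Percentage of 600 simulated trials in which AIC chose intercept-only / linear / quadratic:

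| True change | Outcome SD | ML | REML, months | REML, years |
|---|---|---|---|---|
| none | 5 | 82/11/7 | 99/1/0 | 80/6/13 |
| none | 10 | 77/14/9 | 98/2/0 | 13/0/87 |
| none | 20 | 78/14/8 | 97/3/0 | 0/0/100 |
| 0.3 SD step | 0.6 | 10/19/71 | 90/9/1 | 60/16/24 |
| 0.3 SD step | 5 | 10/20/70 | 71/21/8 | 8/8/85 |
| 0.3 SD step | 10 | 10/19/71 | 64/26/11 | 0/0/100 |
| 0.3 SD step | 20 | 10/18/72 | 49/36/16 | 0/0/100 |
| 0.625 SD step | 0.6 | 0/0/100 | 12/31/56 | 0/3/97 |
| 0.625 SD step | 5 | 0/0/100 | 3/14/83 | 0/0/100 |
| 0.625 SD step | 10 | 0/0/100 | 0/10/90 | 0/0/100 |
| 0.625 SD step | 20 | 0/0/100 | 0/6/94 | 0/0/100 |

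Further runs agreed. For the 0.3 SD step in months, intercept-only was chosen in about 48-89% across SDs of 20 down to 1. For the 0.625 SD step in months it was 0-9%. With no change and time in years, the quadratic was chosen in 91% at SD 10 and 100% at SD 20.

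BIC (penalty on the log number of observations) shows the first error more than the second. For the 0.3 SD step in months, REML-BIC chose intercept-only in 84-98% (ML 54-59%). With no change and time in years it chose the quadratic in only 1% (SD 10) and 4% (SD 20).

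**The case against.** There are three serious replies.

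First, this may be condensed wording. In Main Analyses the comparison and the estimator stand in separate sentences, and only the Abstract fuses them. Naming REML as the estimator is common shorthand, and some R comparison functions refit by ML without being asked. It is therefore true that the computation finally run is unknown. But no function is named, so a refit cannot be assumed. The Abstract also states a method for the comparison, and that method is wrong. This is not a detail merely left to an analysis plan.

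Second, a reader might infer that REML comparison usually favours no change. The figures do not support that. With time in months, intercept-only wins often when the true effect is small, but at the planned f=0.25 it is chosen in under about 10% of trials for SDs of 1 to 20 (12% at SD 0.6). With time in years and an SD of 10 or more, AIC errs the other way, towards curvature that is not there. The percentages depend heavily on the outcome SD, which the article does not give, so no single figure should be quoted without its SD.

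Third, a reader might infer that the lowest index alone decides whether a time effect exists. The article says only that the models are compared, using indices that include these two. It does not say that estimates and tests of the time terms are set aside. This objection stands: the comparison informs the choice of trajectory, and the text goes no further.

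**Conclusion.** The concern holds as a stated method that is invalid: AIC and BIC on REML fits cannot rank models with different fixed effects. The shifts of 0, -4.97 and -14.91 from months to years are exact. They do not depend on the assumed correlation or SD, provided that the random-effects structure is itself unaffected by rescaling time. They show that the ranking is arbitrary, not that it leans in one direction.

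The size of the practical error depends on the assumptions listed above. It can be large in either direction for small or null effects and is modest for the planned effect with time in months. No data are affected, and Results says that analysis follows study completion, so the plan can still be corrected.

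**What to change.** State in Main Analyses that the candidate fixed-effect structures will be fitted by maximum likelihood (REML = FALSE or its equivalent in the package used), with the same random-effects structure, and that AIC and BIC will be computed from those fits. The retained model is then refitted by REML for estimates and confidence intervals. Correct the Abstract's Methods statement to match, and set ML explicitly in the code, since AIC and BIC called on a REML fit use the REML likelihood. Stating the unit of time would help readers, although ML comparisons do not depend on it.

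The cost is about one sentence in each place and one argument in the R code. No data, visits or participants are affected.
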